## Abstract

**Background:**

Evidence showed that Tai Chi may have beneficial effects among hypertensive individuals, although the results are not convincing. We aim to conduct a high-quality clinical trial with 24-h BP measurement to provide robust evidence of Tai Chi for essential hypertension.

**Methods:**

This is an open-label single-center randomized controlled trial with 3 parallel arms. We will compare Tai Chi with walking and waiting-list control. We will recruit 234 hypertensive patients with mild to moderate essential hypertension and randomly assign them to 3 different groups. Participants in Tai Chi group will receive a group-format Yang style 24-form Tai Chi exercise program, 3 sessions per week for 12 weeks. The walking group will be asked to walk, 3 sessions per week for 12 weeks. The waiting-list group will not receive any interventions and/or exercise training. The primary outcome is the change in average 24-h systolic blood pressure (SBP) between baseline and 12 weeks after randomization. The secondary outcomes include 24-h Diastolic Blood Pressure (DBP), average SBP and average DBP during the daytime and night-time, blood pressure (BP) variability, SBP load and DBP load, circadian rhythm of BP, and morning BP surge, endothelial functional indicators, home measured BP, quality of life, adverse events and so on.

**Discussion:**

We expect findings of this trial will provide important insight into application of Tai Chi as an effective and acceptable method for hypertensive patients. Successful completion of this proposed study will also contribute to promotion of Tai Chi in the community in the future.

**Trial registration:**

Clinicaltrials.gov registry: https://clinicaltrials.gov/ct2/show/NCT04267471, date: February 12, 2020.

## Background

Hypertension is the most common risk factor of stroke and cardiovascular diseases, which accounted for 9.4 million deaths worldwide every year [1, 2]. The vast majority of instances of high blood pressure pertains to essential hypertension, which is the presence of high blood pressure while there is no detectable medical or organic cause. According to the World Health Organization report, hypertension affects 22% of adult population around the world [3], and studies showed that the number of hypertensive patients was still increasing [4]. A national wide hypertension survey from 2012 to 2015 reported that the prevalence of hypertension among Chinese population was 23.2% (estimated 244.5 millions people) [5]. Even so, the control rate of hypertension is quite poor. A cross-sectional study of 57,840 hypertensive patients from 17 countries showed that the awareness rate of hypertension was 46.5%, merely 41% received treatment, and only 13.2% had blood pressure (BP) under controll [6]. Pharmacological therapies are the mainstream treatment for hypertension. However, Cochrane reviews showed that many patients discontinued treatment due to undesirable adverse effects [7, 8].

Evidence showed that regular physical exercise had protective effects on hypertensive individuals [9]. Aerobic activity has been recommended to hypertensive patients by Canadian Hypertension Education Program (CHEP), Eighth Joint National Committee (JNC-8), and American Heart Association (AHA) [10–12]. Tai Chi, a traditional mind-body Chinese exercise, is an aerobic exercise with moderate exercise intensity [13]. It combines deep-breath relaxation and gentle movements in sequence with mind concentration. A number of clinical trials reported that Tai Chi not only had positive effects in healthy population [14–17], it could also improve people’s pathological conditions, including Parkinson’s disease [18], fibromyalgia [19] and knee osteoarthritis [20].

Several clinical studies reported that Tai Chi may have some benefits in reducing BP and improving quality of life in hypertensive patients [21–27]. We conducted a systematic review of the existing trials of Tai Chi for essential hypertension [28]. However, we found high heterogeneity and poor methodological quality in these studies, which decreased the liability of evidence. Therefore, we will conduct this randomized controlled trial (RCT) aiming at: first, confirming whether Tai Chi is efficacious for patients with essential hypertension; second, observing the short- and long-term effect of Tai Chi; third, investigating the influence of Tai Chi on endothelial function. In addition, we intend to use 24-h BP measurement to monitor patients’ BP, so as to observe the changes more accurately. In order to provide high quality of evidence, we will conduct this trial in line with Standard Protocol Items: Recommendations for Interventional Trials (SPIRIT) [29] and report our findings in accordance with the Consolidated Standards of Reporting Trial (CONSORT) statement [30]. This clinical trial is registered with an identifier (NCT04267471) at clinicaltrials.gov in February 2020.

## Methods/design

### Design and setting

This is an open-label single-center RCT with 3 parallel arms. This trial has been approved by the regional ethical review committee of traditional Chinese medicine in Sichuan Province in March 2019 (reference number: 2019KL-001). We will compare Tai Chi with walking and waiting-list control. The trial will be conducted in the Hospital of Chengdu University of Traditional Chinese Medicine. The whole study period is 25 weeks, with 1-week baseline, 12-week intervention phase and 12-week follow-up phase. After randomization, participants in Tai Chi group and walking group will receive exercise training 3 times per week for continuous 12 weeks. Participants in waiting-list group can decide whether or not to receive exercise training after follow-up period. Outcomes will be measured at baseline, 12 weeks and 24 weeks after randomization. All participants will be required to sign the written informed consent before randomization. This protocol was compiled in line with the SPIRIT 2013 [29] (Table 1). The flow diagram of this trial is presented in Fig. 1.

**Table 1 Tab1:**
[figure not shown]
A standard protocol items: recommendation for interventions for trials (SPIRIT)

*BP* Blood pressure, *NO* Nitric Oxide, *ET* Endothelin, *TXA2* Thromboxane A2, *VEGF* Vascular endothelial growth factor, *SF-36* Medical Outcomes Study 36-Item Short Form

**Fig. 1 Fig1:**
[figure not shown]
Flow diagram of study design

### Participants

#### Sample size

This study is an RCT, the intervention group is the Tai Chi group, and the control groups are walking group and waiting-list group. The reduction of Systolic Blood Pressure (SBP) is set as the primary outcome. According to previous study [31], the mean difference and standard deviation of SBP was − 13.33 ± 46.73, − 12.46 ± 33.37 and 3.37 ± 46.01 for Tai Chi compared with walking and waiting-list control. The sample size was calculated using One-Way analysis of variance, F-Tests with the PASS 15.0 software. The standard deviation is set as 20. A total of 65 participants per arm are needed to achieve a power of 80% at a significant level of 5%. A sample size of 195 participants is required to sufficiently detect a target effect size. Considering a 20% drop-out rate, we intend to enroll a total of 234 participants, with 78 participants in each group.

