### Allocation and randomization

Included participants will be randomly assigned to 3 groups (Tai Chi group, walking group, and waiting-list group) with 1:1:1 ratio. The randomization sequence will be created using R 3.5.1 by an independent statistician. The information of random numbers, allocation and intervention will be packed in opaque envelopes, and will be concealed to screeners and outcome assessors. A research assistant will inform eligible participants the allocation results through phone call after opening envelopes in order.

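### The stated 65 per arm does not reproduce from the printed means with SD 20 (they need 23), but does if the waiting-list value is −3.37; the SD of 20 is also unexplained

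*Protocol article*

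**What the plan says.** All the inputs stand in the Sample size section of the protocol article.

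- **Effect and source SDs:** "the mean difference and standard deviation of SBP was − 13.33 ± 46.73, − 12.46 ± 33.37 and 3.37 ± 46.01", attributed to a previous study. The first two values carry a minus sign and the third does not.
- **Method:** "The sample size was calculated using One-Way analysis of variance, F-Tests with the PASS 15.0 software".
- **Planning SD and result:** "The standard deviation is set as 20. A total of 65 participants per arm are needed to achieve a power of 80"%, at the 5% level. No reason is given for the SD. The section continues with "A sample size of 195 participants is required to sufficiently detect a target effect size", and the number is then raised to 78 per arm for drop-out.

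The Allocation and randomization section confirms equal arms ("with 1:1:1 ratio"). The Primary outcome section defines the endpoint as the 12-week change in average 24-h ambulatory SBP.

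**The concern.** The section prints every input that a one-way ANOVA sample size needs, together with the result. The result should therefore follow from the inputs, and it does not. Two things need explaining.

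1. The printed means with SD 20 describe a large effect that needs far fewer than 65 per arm.
2. The SD of 20 is smaller than every SD quoted in the sentence before it, and less than half of two of them.

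What is at stake is the meaning of the stated 80% power. A reader cannot tell which between-arm difference the trial was sized for, or why the variability of the source study was set aside. Both matter when a null result is interpreted.

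**Working it through.** **Inputs** (Sample size section): k = 3 equal arms, two-sided F-test at α = 0.05, target power 80%, SD σ = 20, means as printed. The text introduces the values with "the mean difference and standard deviation of SBP was", so treating them as one mean change per arm (Tai Chi, walking, waiting list) is an assumption.

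**Formula.** With n per arm, the noncentrality is λ = n·Σ(μᵢ − μ̄)²/σ². Power is P(F′ > F₀.₉₅), with F′ noncentral F on 2 and 3(n − 1) degrees of freedom. The effect size is f = √(Σ(μᵢ − μ̄)²/3)/σ.

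**Step 1: values as printed (−13.33, −12.46, +3.37), SD 20.**
- μ̄ = −22.42/3 = −7.473.
- Squared deviations 34.30 + 24.87 + 117.58 = 176.75.
- f = √(176.75/3)/20 = 7.676/20 = 0.384.
- n = 22 gives 78.3% power and n = 23 gives 80.3%, so **23 per arm** are needed.
- At n = 65, λ = 65 × 176.75/400 = 28.7 and power is **99.9%**.

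The stated 65 is not reproduced.

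**Step 2: third value as −3.37, everything else unchanged.**
- μ̄ = −29.16/3 = −9.72.
- Squared deviations 13.03 + 7.51 + 40.32 = 60.86.
- f = 4.504/20 = 0.225.
- n = 64 gives 79.8% power. n = 65 (λ = 65 × 60.86/400 = 9.89) gives **80.4%**.

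The stated 65 is reproduced to the participant.

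**Step 3: the target difference under each sign (Tai Chi versus waiting list).**
- As printed: 3.37 − (−13.33) = 16.70 mmHg.
- With −3.37: −3.37 − (−13.33) = 9.96 mmHg.

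**Step 4: other readings of the three values.** Taking two of them as differences from a reference arm at zero also fails to give 65 at SD 20:
- arms at 0, 13.33 and 12.46 need 36 per arm;
- arms at 0, 12.46 and −3.37 need 29;
- arms at 0, −13.33 and 3.37 need 26.

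**Step 5: the SD.** The pooled source SD is √((46.73² + 33.37² + 46.01²)/3) = √1804.7 = 42.48. The same F-test gives:

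| SD | n per arm for 80%, +3.37 | Power at 65, +3.37 | n per arm for 80%, −3.37 | Power at 65, −3.37 |
|---|---|---|---|---|
| 20 (planning) | 23 | 99.9% | 65 | 80.4% |
| 33.37 (smallest quoted) | 62 | 82.2% | 178 | 36.9% |
| 42.48 (pooled) | 100 | 60.4% | 287 | 24.1% |
| 46.73 (largest quoted) | 121 | 51.9% | 347 | 20.5% |

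**The case against.** The strongest defence is that the calculation was done correctly and only the text is wrong. An exact match at 65, with the stated test, SD, level and power, is unlikely to be chance. The section also describes the outcome as a reduction in SBP, and reductions of 13.33, 12.46 and 3.37 give the same 65. On this view a single minus sign went missing, and 65 with 80% power is right for SD 20.

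Most of this stands. It shows that the stated size is not arbitrary, and it rules out the inference that 65 could come only from some unstated SD (with the printed means it would take about 34). It does not settle the sign. The other two values are printed as negative changes, so an unsigned 3.37 beside them reads as a rise. A wrong sign typed into the software would produce the same 65. If −3.37 is right, the printed text still overstates the target difference by 16.70 − 9.96 = 6.74 mmHg.

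On the SD, the defence is that the source figures are described only as SBP, whereas this trial's endpoint is the change in mean 24-h ambulatory SBP, analysed by ANCOVA with pre-intervention BP as a covariate. An SD of 20 may therefore be reasonable. That also stands as a possibility, but the protocol does not make the argument. It places 20 directly after three larger SDs and gives no reason.

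**Conclusion.** The sample size does not reproduce as printed: the printed inputs need 23 per arm, not 65. The most likely cause is a sign inconsistency on the waiting-list value, since −3.37 gives exactly 65 with 80.4% power. The document alone cannot show whether the text or the calculation carries the wrong sign. The planning SD of 20, below every quoted SD, is a separate gap in justification.

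A reader might infer that the trial is clearly underpowered. The documents do not support that. At the planning SD, 65 per arm gives 80.4% or 99.9% power, depending on the sign. The lower figures (60% or 24% at the pooled SD) hold only if the source SDs apply to the change in 24-h ambulatory SBP, which nothing in the protocol shows. Nor does it follow that the trial is nearly three times too large: that takes the printed plus sign as certain.

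The conclusion assumes one mean change per arm and the unadjusted one-way F-test that the section names.

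**What to change.** Keep 65 evaluable per arm and revise the Sample size paragraph:

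1. Say plainly whether the three values are mean changes per arm. Check the sign of 3.37 against the source study and the software input, and correct whichever is wrong.
2. If −3.37 is right, correct the printed value; the 65 and the 80% then stand for SD 20. If +3.37 is right, restate the power (99.9% at SD 20) or state the smaller target effect that 65 per arm detects with 80% power.
3. Give the reason for assuming SD 20 for the 12-week change in 24-h ambulatory SBP in place of the quoted SDs.
4. Show power at 65 per arm over a range of plausible SDs, as in the table above.

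The calculation should be reconciled, not removed. The cost is rewording and one look at the source and the software file, with no extra patients. The stated power may look less favourable once the range of SDs is shown.

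### The enrolment of 234 allows for a 16.7% drop-out rate, not the stated 20%, which would leave about 187 completers against the 195 called for (minor)

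*Protocol article*

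**What the plan says.** The Sample size section of the protocol article names the method: "The sample size was calculated using One-Way analysis of variance, F-Tests with the PASS 15.0 software". It fixes the spread ("The standard deviation is set as 20") and gives the result per arm: "A total of 65 participants per arm are needed to achieve a power of 80% at a significant level of 5"%. The total follows: "A sample size of 195 participants is required to sufficiently detect a target effect size". The allowance for losses comes last: "Considering a 20% drop-out rate, we intend to enroll a total of 234 participants, with 78 participants in each group".

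The Methods part of the abstract repeats the enrolment figure ("We will recruit 234 hypertensive patients with mild to moderate essential hypertension"), and the Allocation and randomization section assigns participants "with 1:1:1 ratio". Nothing in the article defines the 20% as a share of the required number. The section on attendance and drop-outs uses the term for participants who leave the trial, that is, a fraction of those enrolled.

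**The concern.** An allowance for drop-out is made so that the required number remains after the losses. To do that, the required number is divided by the proportion expected to stay. Here it was multiplied by one plus the drop-out rate, which always gives too few. The paragraph therefore contains three statements that cannot all be true: 195 are required, 20% will be lost, and 234 will be enrolled. At stake is whether the trial keeps, at its own assumed loss, the number of participants on which it bases its power statement.

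**Working it through.** **Inputs**, all from the Sample size section except the allocation ratio, which is in Allocation and randomization: 65 required per arm; 195 required in total; drop-out 20%; 234 enrolled, 78 per arm; three arms at 1:1:1; one-way F-test, 80% power, 5% level.

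**1. Reproduce the plan's figure.**
- Per arm: 65 × 1.2 = 78.
- Total: 195 × 1.2 = 234.

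Both match exactly, so the rule used was n × (1 + d).

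**2. Apply the stated loss to those enrolled.**
- Per arm: 78 × 0.8 = 62.4.
- Total: 234 × 0.8 = 187.2.
- Shortfall: 195 − 187.2 = 7.8 in total; 65 − 62.4 = 2.6 per arm.

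**3. Find the loss that 234 does cover.**
- 1 − 195/234 = 39/234 = 0.167, or 16.7%.

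**4. Find the enrolment that matches 20%.** The formula is n / (1 − d).
- Total: 195/0.8 = 243.75, rounded up to 244.
- Per arm: 65/0.8 = 81.25, rounded up to 82, which gives 3 × 82 = 246.

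Since 244 does not divide by three, 246 is the figure that fits equal allocation. It is 12 more than 234.

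**5. Size the effect on power.** The calculation uses the non-central F distribution with three groups, degrees of freedom 2 and 3n − 3, and non-centrality 3nf², where n is the number per arm and f is Cohen's effect size.
- Setting power to exactly 80% at n = 65 gives 3f² = 0.1506, so f = √(0.1506/3) ≈ 0.224.
- At n = 62 with the same f, power is 77.9%.
- At n = 62.4, power is 78.2%.

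The loss is about 2 percentage points.

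**6. Why f was solved backwards.** The printed inputs do not lead to 65. Taking −13.33, −12.46 and 3.37 as the three group means with SD 20, the F-test needs 23 per arm for 80% power and has 99.8% power at 62. If the third value is read as −3.37, a sign the article does not print, power is 79.8% at 64, 80.4% at 65 and 78.4% at 62, so 65 would be the smallest sufficient number. That reading is plausible but is a conjecture. The figure of about 78% in step 5 does not depend on it. Steps 1 to 4 use no means or SD at all.

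**The case against.** The strongest reply is that nobody is lost from the analysis. The Statistical analysis section specifies intention-to-treat with last observation carried forward, and 24-hour systolic pressure is measured at baseline. Every randomised participant with a baseline reading, up to 78 per arm, would then formally enter the primary comparison. A reader who concluded that the trial will be analysed on 62 per arm would be going beyond the document. This part of the reply stands.

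It does not rescue the allowance. Ambulatory pressure is measured only at baseline, 12 weeks and 24 weeks, so a participant lost before week 12 has a carried-forward change of zero rather than an observed outcome. If such records counted as fully informative, no allowance for drop-out would have been needed. The plan made one so that 195 would remain.

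Three further replies limit the size of the point, and they stand:
- The 20% is a planning guess with no source given in the Sample size section, and the gap between 16.7% and 20% is within the uncertainty of such a guess.
- The planned analysis is an ANCOVA with pre-intervention blood pressure among its covariates, whereas the sizing used an unadjusted F-test. A 2-point loss on that F-test is not the power of the planned analysis.
- The endpoint, the test and the type I error rate are not affected.

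**Conclusion.** The statement is wrong as written, and the matter is minor. With 65 per arm required and 234 enrolled, the drop-out rate covered is 16.7%. With 20% drop-out, about 187 completers remain (62 per arm), about 8 short of 195. These figures follow from the printed numbers by arithmetic alone.

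The power figure of about 78% is less firm. It assumes that 65 per arm gives exactly 80% power, it counts completers only, and it refers to the one-way F-test used for sizing.

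A reader might infer that the trial is seriously underpowered, or that a fall from 80.4% to 78.4% can be read off the article's own inputs. The documents support neither. The gap is 2 to 3 participants per arm, and the second pair of figures needs a minus sign that is not printed. That 65 is not reproduced from the printed means with SD 20 is a separate question, and this point takes 65 as given.

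**What to change.** Restate one figure in the Sample size section. Either of these is correct:
- 234 participants (78 per arm) allow for a drop-out rate of 16.7%.
- With 234 participants, a 20% drop-out rate leaves about 62 completers per arm, with power of about 78% on the one-way F-test, taking 65 per arm as giving 80%.

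The cost is one sentence and a slightly less favourable claim. The design and the enrolment figure in the abstract stay as they are. For reference only, the total that matches 20% drop-out and 65 completers per arm at equal allocation is 246 (82 per arm); adopting it would mean 12 more participants and a change to the abstract as well.

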#### Recruitment

Participants will be recruited by posters, doctor’s recommendation, internet and WeChat in Chengdu city. If participants meet the study criteria, they will be required to sign informed consent form prior to inclusion of the study.

#### Diagnostic criteria

According to the 2010 Chinese Guidelines for the Management of Hypertension [32], patients with SBP ≥ 140 mmHg and/or Diastolic Blood Pressure (DBP) ≥ 90 mmHg without using antihypertensive drugs for 3 times on different days are diagnosed with hypertension. The patient who has a history of hypertension and is currently using antihypertensive drugs with BP below 140/90 mmHg is also diagnosed with hypertension. All patients will be diagnosed by 2–3 cardiovascular physicians with more than 10 years of experience.

#### Inclusion criteria

Patients who fulfill all the following inclusion criteria will be included in this study:
aged between 45 to 80 years;diagnosed with mild to moderate essential hypertension, and meet the diagnostic criteria of mild to moderate essential hypertension according to 2010 Chinese Guidelines for the Management of Hypertension (140 mmHg≤SBP ≤ 169 mmHg and/or 90 mmHg≤DBP ≤ 109 mmHg) [31];with or without antihypertensive medication;with no regular exercise in the past 3 months;willing to comply with the study protocol;willing to sign informed consent form.

#### Exclusion criteria

Patients with one of the following criteria will be excluded:
diagnosed with secondary hypertension or refractory hypertension [33];with severe medical visceral condition and chronic diseases, such as diabetes, epilepsy, severe depression or anxiety, psychosis;with severe bone and joint diseases or motor dysfunction limit ability to participant exercise;with severe cognitive decline (Montreal Cognitive Assessment, MoCA [34], < 26)with decreased myodynamia, poor balance or limited vision that would impede full participation in the study;participated in other clinical trials at the same time.

### Allocation and randomization

Included participants will be randomly assigned to 3 groups (Tai Chi group, walking group, and waiting-list group) with 1:1:1 ratio. The randomization sequence will be created using R 3.5.1 by an independent statistician. The information of random numbers, allocation and intervention will be packed in opaque envelopes, and will be concealed to screeners and outcome assessors. A research assistant will inform eligible participants the allocation results through phone call after opening envelopes in order.

